### Treatment protocol

All enrolled patients will receive definitive CCRT as the initial treatment according to institutional standard protocols based on international guidelines. External beam radiotherapy (EBRT) will be delivered using 6-megavolt (MV) X-ray volumetric modulated arc therapy (VMAT) technique on a linear accelerator. Target volume delineation will be performed according to the European Society for Medical Oncology (ESMO) Clinical Practice Guidelines for cervical cancer management. The gross tumor volume (GTV) will include the primary cervical tumor and any involved lymph nodes identified on MRI and/or PET-CT. The clinical target volume (CTV) will encompass the GTV plus the parametria, upper vagina (at least 3 cm below the distal extent of the tumor or to the introitus if more distal involvement), uterus, and regional lymph node areas including the common iliac, internal iliac, external iliac, obturator, presacral, and para-aortic lymph nodes (if involved). The planning target volume (PTV) will be created by adding appropriate margins (typically 5–7 mm) to the CTV to account for setup uncertainties and organ motion.

The prescribed dose to 95% of the PTV will be 45–50.4 gray (Gy) administered in 1.8 Gy per fraction, delivered five fractions per week over approximately 5–6 weeks. For patients with FIGO 2018 stage IIIC1 (pelvic lymph node metastases) or IIIC2 (para-aortic lymph node metastases) disease, a simultaneous integrated boost (SIB) technique will be employed to deliver escalated doses to macroscopically involved lymph nodes. Specifically, 95% of the planning gross tumor volume of involved nodes (PGTV_nd) will receive 59.36 Gy in 2.12 Gy per fraction over the same treatment period, achieving a biologically equivalent dose appropriate for nodal disease control while maintaining acceptable doses to organs at risk.

Concurrent platinum-based chemotherapy will consist of cisplatin administered intravenously at a dose of 40 milligrams per square meter (mg/m²) body surface area weekly during the course of EBRT, with a maximum of six cycles. Chemotherapy will be administered on the same day as radiotherapy when possible, typically on Mondays. Dose modifications or delays will be implemented according to standard institutional protocols based on hematologic and non-hematologic toxicity criteria per Common Terminology Criteria for Adverse Events (CTCAE) version 5.0. Specifically, chemotherapy will be held if absolute neutrophil count is<1.5×10^9^/L, platelet count is<75×10^9^/L, or serum creatinine is >1.5 times ULN, and will be resumed when counts recover.

Intracavitary brachytherapy will be initiated in the fourth or fifth week of pelvic EBRT, after the primary tumor has shown adequate response to allow safe applicator insertion. Brachytherapy will be delivered using computed tomography (CT)-guided three-dimensional image-guided adaptive brachytherapy with an iridium-192 (Ir-192) high-dose-rate remote afterloading system. Applicators (tandem and ovoid or tandem and ring) will be placed under appropriate anesthesia, and CT imaging will be performed with the applicator in place for treatment planning. Target volumes will be delineated according to the Groupe Européen de Curiethérapie and European Society for Therapeutic Radiology and Oncology (GEC-ESTRO) recommendations, including the high-risk CTV (HR-CTV) encompassing gross residual disease and the intermediate-risk CTV (IR-CTV). A prescription dose of 7 Gy per fraction to the HR-CTV will be delivered once weekly for a total of four fractions over 2 weeks, with dose-volume constraints respected for organs at risk (bladder, rectum, sigmoid, bowel). The cumulative biologically equivalent dose in 2-Gy fractions (EQD2) for the combination of EBRT and brachytherapy will target ≥85 Gy for HR-CTV and<90 Gy for the bladder and rectum (D2cc).

### Blood sampling and time points for ctDNA detection

Peripheral venous blood samples (10 milliliters [mL] per time point) will be collected into ethylenediaminetetraacetic acid (EDTA)-anticoagulated tubes (Becton Dickinson, Franklin Lakes, New Jersey, USA) at the following predefined time points to capture ctDNA dynamics throughout the treatment course and follow-up period:

T0 (baseline): Within 7 days before initiation of CCRT. This baseline sample will establish the pretreatment HPV ctDNA level as a reference point and will be correlated with baseline tumor burden assessed by imaging and clinical examination.

T1 (mid-treatment): After 3–4 weeks of CCRT (approximately 15–20 fractions of radiotherapy and 3–4 cycles of concurrent chemotherapy).

T2 (end of CCRT): Within 1 week after completion of all CCRT including brachytherapy.

T3 (first evaluation): At 3 months (± 2 weeks) after completion of CCRT, coinciding with the first scheduled imaging assessment.

Follow-up sampling: Every 6 months (± 4 weeks) thereafter for up to 24 months from the completion of CCRT, or until disease progression, death, withdrawal of consent, or study completion, whichever occurs first. Additional blood samples may be collected at unscheduled visits if disease recurrence or progression is clinically suspected, to correlate ctDNA status with disease status.

Blood samples will be processed according to a standardized protocol to ensure consistency and minimize preanalytical variability. Specifically, blood samples must be maintained at room temperature and processed within 2 hours of collection to prevent cell lysis and release of genomic DNA that could dilute ctDNA signals. Samples will be centrifuged at 1,600 × g for 10 minutes at 4 °C to separate plasma from cellular components. The plasma supernatant will be carefully transferred to a new tube without disturbing the buffy coat layer and will be subjected to a second centrifugation at 16,000 × g for 10 minutes at 4 °C to remove any residual cells and debris. The resulting cell-free plasma will be aliquoted into 1-mL cryovials, labeled with unique identifiers, and stored immediately at –80 °C until batch analysis. All samples will be tracked using a laboratory information management system to ensure chain of custody and prevent sample mix-ups.

### ctDNA detection methods

#### DNA extraction

Circulating cell-free DNA (cfDNA) will be extracted from 1–4 mL of frozen plasma samples using the QIAamp Circulating Nucleic Acid Kit (Qiagen, Hilden, Germany, catalog number 55114) according to the manufacturer’s instructions with minor modifications to optimize recovery of low-abundance ctDNA. Briefly, plasma samples will be thawed on ice, and carrier RNA will be added to improve DNA binding to the silica membrane and increase extraction efficiency. After lysis and binding steps, cfDNA bound to the QIAamp Mini column will be washed with proprietary wash buffers to remove contaminants, and cfDNA will be eluted in 30–50 microliters (μL) of elution buffer. The concentration and quality of extracted cfDNA will be assessed using the Qubit dsDNA High Sensitivity Assay Kit (Thermo Fisher Scientific, Waltham, Massachusetts, USA) on a Qubit 4 Fluorometer. Extracted cfDNA will be stored at –80 °C and subjected to no more than two freeze-thaw cycles before analysis to maintain DNA integrity.

#### Plasma HPV ctDNA detection by droplet digital PCR and exploratory NGS

ctDNA will be quantified using a validated multiplex ddPCR assay targeting the E6/E7 regions of HPV16 and HPV18, the two most common high-risk HPV types associated with cervical cancer. ddPCR provides absolute quantification without standard curves, offering high sensitivity and precision for low-abundance targets. All analyses will be performed at the Molecular Diagnostics Laboratory, Shanghai MedTech Bio-Molecular Testing Center, using the AccuONE-R300PB chip-based system with multiplex detection of HPV16, HPV18, and a human internal reference gene (ER) to ensure sample quality and normalize DNA input. Stringent quality control measures, including no-template and positive controls, will be applied, and samples failing QC or with insufficient droplet counts will be repeated. HPV ctDNA concentrations will be calculated as copies per milliliter of plasma. ctDNA positivity will be determined according to the prespecified analytical criteria of the validated ddPCR assay, including the limit of blank (LoB), limit of detection (LOD), limit of quantification (LOQ), droplet quality metrics, and negative and positive controls. Samples with HPV16/18 E6/E7 signals reaching or exceeding the assay-defined LOD/LOQ will be classified as ctDNA-positive/detectable, whereas samples with no HPV16/18 signal or signals not exceeding the LoB will be classified as ctDNA-negative/undetectable (18, 19). Trace-positive results will be defined as low-level HPV16/18 signals above the assay background or LoB but below the assay-defined LOD/LOQ, or as low-copy signals that do not meet the predefined criteria for reliable quantification (18). These samples will be repeated when sufficient residual cfDNA is available and will be reported separately. In the primary analysis, trace-positive samples will not be considered definitively ctDNA-positive. If trace-positive results are observed, an exploratory sensitivity analysis will be conducted by reclassifying these samples as ctDNA-positive to assess whether their classification affects the primary findings. Exploratory targeted NGS will be performed in approximately 20 patients to validate ddPCR findings and explore additional tumor-specific genomic alterations. Patients with detectable or trace-positive HPV ctDNA at 3 months after CCRT, disease recurrence or progression during follow-up, or high baseline ctDNA levels will be prioritized. Approximately one-third of the NGS subset will be selected from patients with undetectable ctDNA at 3 months, balanced by FIGO stage, histological subtype, and baseline HPV16/18 status. NGS findings will be exploratory and used for assay cross-validation and hypothesis generation rather than formal subgroup inference. Detailed procedures for cfDNA extraction, assay setup, primer/probe sequences, thermal cycling, quality control, quantification formulas, and NGS methods are provided in the Supplementary Materials.

### Clinical evaluation and imaging

Treatment response will be assessed at 3 months (± 2 weeks) after completion of CCRT using pelvic MRI as the primary imaging modality, supplemented by PET-CT in selected cases based on clinical indication (such as suspected distant metastases or equivocal MRI findings). MRI will be performed using a 1.5-Tesla or 3-Tesla scanner with appropriate pelvic coils, and will include multiparametric sequences such as T2-weighted imaging in axial, sagittal, and coronal planes, T1-weighted imaging, diffusion-weighted imaging (DWI) with apparent diffusion coefficient (ADC) mapping, and dynamic contrast-enhanced (DCE) imaging. Tumor response will be evaluated according to Response Evaluation Criteria in Solid Tumors (RECIST) version 1.1, with complete response (CR) defined as disappearance of all target lesions, partial response (PR) as at least a 30% decrease in the sum of diameters of target lesions, progressive disease (PD) as at least a 20% increase in the sum of diameters of target lesions or appearance of new lesions, and stable disease (SD) as neither sufficient shrinkage to qualify for PR nor sufficient increase to qualify for PD.

Follow-up imaging will be performed every 6 months (± 4 weeks) for the first 2 years, then annually for years 3–5, or more frequently if clinically indicated based on symptoms suggestive of disease recurrence (such as abnormal vaginal bleeding, pelvic pain, or new onset of symptoms). Additional imaging studies such as chest CT, abdominal CT, or bone scintigraphy may be performed at the discretion of the treating physician if metastatic disease is suspected. All imaging studies will be reviewed by radiologists with expertise in gynecologic oncology who are blinded to ctDNA results, and findings will be documented using standardized radiology report templates. Imaging-detected disease recurrence will be confirmed by biopsy whenever feasible and clinically appropriate to obtain histopathologic confirmation.

### Outcome measures

The primary outcome of this study is progression-free survival (PFS), defined as the time from the date of initiation of CCRT to the date of first documented disease progression (according to RECIST 1.1 criteria on imaging studies or histopathologic confirmation), disease recurrence (appearance of new lesions after achieving CR), or death from any cause, whichever occurs first. Patients who are alive and progression-free at the time of analysis will be censored at the date of their last adequate tumor assessment.

Secondary outcome include: (1) Overall survival (OS), defined as the time from the initiation of CCRT to death from any cause, with patients who are alive at the time of analysis censored at the date they were last known to be alive; (2) Objective response rate (ORR), defined as the proportion of patients achieving CR or PR at the first imaging assessment (3 months post-CCRT) according to RECIST version 1.1 criteria; (3) Dynamic changes in plasma HPV ctDNA levels expressed as continuous variables (copies per mL) and categorical variables (detectable versus undetectable) at predefined time points (T0, T1, T2, T3, and follow-up time points) during and after CCRT, including assessment of ctDNA clearance kinetics (time to first undetectable ctDNA), nadir ctDNA levels, and patterns of ctDNA dynamics (rapid clearance, slow clearance, persistent detection, or reappearance after initial clearance); (4) Predictive performance of HPV ctDNA for disease recurrence, including calculation of sensitivity (proportion of patients with recurrence who have detectable ctDNA), specificity (proportion of patients without recurrence who have undetectable ctDNA), positive predictive value (PPV; probability of recurrence given detectable ctDNA), negative predictive value (NPV; probability of no recurrence given undetectable ctDNA), and area under the receiver operating characteristic curve (AUC-ROC) for ctDNA as a predictive biomarker, with 95% confidence intervals (CIs); and (5) Concordance between HPV ctDNA status and imaging-based assessment (MRI and/or PET-CT) in detecting residual disease at 3 months post-CCRT and early relapse during follow-up, assessed using Cohen’s kappa statistic and contingency table analysis. Additionally, we will explore the lead time advantage of ctDNA detection, defined as the time interval between ctDNA-detected recurrence and imaging-detected recurrence in patients who experience disease progression (20). The detailed schedule of assessments follows the SPIRIT framework and is presented in **Table 1**, which outlines all study procedures, evaluations, and time points from screening through close-out.

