**Methods/design:**

This single-center, observational cohort study will enroll 57 patients with histologically confirmed LACC (FIGO 2018 stage IB2–IVA) and baseline high-risk HPV infection. All patients will receive standard CCRT including external beam radiotherapy (45–50.4 Gy), concurrent weekly cisplatin (40 mg/m²), and intracavitary brachytherapy. Peripheral blood samples (10 mL) will be collected at five predefined time points: baseline (T0), mid-treatment (T1), end of CCRT (T2), 3 months post-CCRT (T3), and every 6 months thereafter for 24 months. Plasma HPV ctDNA will be quantified using droplet digital PCR targeting HPV16/18 E6/E7 genes. The primary endpoint is progression-free survival (PFS), comparing patients with detectable versus undetectable ctDNA at 3 months post-CCRT.

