### Sample size calculation

The sample size was calculated based on the primary endpoint of 2-year progression-free survival (PFS), comparing patients with detectable versus undetectable plasma HPV ctDNA at 3 months after completion of CCRT (T3). Institutional historical data indicate a 2-year PFS of approximately 75% in the ctDNA-negative group, while published studies suggest a rate of approximately 50% in the ctDNA-positive group (21). Based on prior studies of HPV-associated malignancies, we conservatively estimated that 30% of patients would be ctDNA-positive at the T3 assessment. Sample size was estimated using the log-rank test for comparing survival curves between two groups: 
$\text{n}={\left({\text{Z}}_{1}-\alpha {/}_{2}+{\text{Z}}_{1}-\beta \right)}^{2}/\left[{\left(\ln\text{HR}\right)}^{2}\times \text{p}\left(1-\text{P}\right)\right]$.

where 
$Z_{1-\alpha /2}=1.96$ for a two-sided α = 0.05, 
$Z_{1-\beta }=0.842$ for 80% power, and *p* = 0.30 represents the proportion of patients expected to be ctDNA-positive. The hazard ratio (HR) was derived from the assumed survival probabilities (
$S_{\text{ctDNA}+}=0.50$, 
$S_{\text{ctDNA}-}=0.75$), yielding an estimated HR of 2.41. Using these assumptions, a minimum of 48 evaluable patients is required to achieve 80% power to detect a difference in 2-year PFS at a two-sided significance level of 0.05. Allowing for an anticipated 15% attrition rate, the total target enrollment is 57 patients. This sample size is considered feasible for recruitment at a single high-volume tertiary cancer center over the planned 2-year enrollment period and is supported by effect sizes reported in prior studies of ctDNA as a prognostic biomarker in HPV-associated cancers (21, 22).

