### Statistical analysis

All statistical analyses will be performed using SPSS v27.0 (IBM Corp., USA) and R v4.3.0 or later. Baseline characteristics will be summarized using descriptive statistics: continuous variables as mean ± SD or median (IQR) depending on normality, and categorical variables as frequencies and percentages. Group comparisons (ctDNA-positive vs ctDNA-negative) will use Student’s t-test or Mann-Whitney U test for continuous variables, and χ² or Fisher’s exact test for categorical variables.

Longitudinal ctDNA changes will be analyzed using generalized estimating equations (GEE) or linear mixed-effects models to account for repeated measures, adjusted for baseline covariates such as FIGO stage, tumor size, and nodal status. PFS and OS will be estimated by Kaplan-Meier method and compared with log-rank tests; hazard ratios (HRs) with 95% CIs will be obtained from univariate and multivariate Cox proportional hazards models. Covariates in multivariate models will be checked for collinearity (VIF >5) and proportional hazards assumption (Schoenfeld residuals).

Predictive performance of ctDNA for recurrence will be evaluated using ROC curves (AUC, sensitivity, specificity, PPV, NPV); optimal cut-offs for continuous ctDNA will be determined via Youden’s index. Concordance between ctDNA and imaging will be assessed with Cohen’s kappa. Missing data<20% will be handled by multiple imputation (MICE), with sensitivity analyses including complete-case analyses. Patients lost to follow-up will be censored at the last known date. Two-sided p-values<0.05 indicate statistical significance, with multiple testing correction applied for secondary endpoints. Exploratory subgroup analyses may be conducted by FIGO stage, histology, or baseline HPV type. These subgroup analyses will be exploratory and hypothesis-generating and will not be used for confirmatory subgroup inference.

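### Primary PFS is timed from the start of CCRT but compared by T3 ctDNA status with no landmark, so progression found at or before the T3 scan counts as predicted by a same-day or later sample

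*Protocol article*

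**What the plan says.** All references are to the protocol article.

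- **Clock.** Outcome measures gives PFS as "defined as the time from the date of initiation of CCRT to the date of first documented disease progression", with recurrence and death from any cause also counting as events.
- **Groups.** The abstract (Methods/design) states the primary comparison as "comparing patients with detectable versus undetectable ctDNA at 3 months post-CCRT". Sample size calculation repeats it: "comparing patients with detectable versus undetectable plasma HPV ctDNA at 3 months after completion of CCRT (T3").
- **Timing of T3.** Blood sampling and time points places it "At 3 months (± 2 weeks) after completion of CCRT, coinciding with the first scheduled imaging assessment". Table 1 shows no RECIST evaluation before that visit.
- **Analysis.** Statistical analysis names Kaplan-Meier curves, log-rank tests and Cox models. It mentions no landmark, delayed entry or time-dependent ctDNA covariate.
- **Early failures.** Withdrawal criteria lists progression during CCRT as a ground for withdrawal and keeps data collected up to withdrawal in the analysis. On missing values, the plan states "Missing data<20% will be handled by multiple imputation (MICE"), with complete-case sensitivity analyses.
- **Two-year PFS.** Sample size calculation uses 75% and 50% by T3 status without saying from which date the two years run.

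**The concern.** A patient's group is unknown until T3, yet events count from the first day of CCRT. Three kinds of patient are affected:

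- A patient with progressive disease on the T3 scan has the event at about the moment the group is assigned. Because this is the first scheduled response scan, early failures will tend to be dated here.
- A patient who progressed earlier but is still sampled at T3 is classified after the event.
- A patient who died before T3 has no T3 status.

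In the first two cases, a positive sample agrees with disease already visible; it does not forecast anything. The protocol has a separate secondary outcome for that agreement, the concordance of ctDNA with imaging at 3 months (Outcome measures, item 5). At stake is the meaning of the primary hazard ratio: it could look prognostic even if T3 ctDNA said nothing about the course of patients who are progression-free at T3.

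**Working it through.** **1. Gap between clock start and T3.** EBRT is "delivered five fractions per week over approximately 5–6 weeks". Brachytherapy "will be initiated in the fourth or fifth week of pelvic EBRT" and is given "once weekly for a total of four fractions over 2 weeks". That last phrase does not agree with itself and needs reconciling; here it only means that CCRT length must be assumed, and I take 6 to 8 weeks. With 4.345 weeks per month:

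- 6/4.345 + 3 = 4.4 months; 8/4.345 + 3 = 4.8 months.
- With the ±2-week window: 4/4.345 + 3 = 3.9 to 10/4.345 + 3 = 5.3 months.

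**2. The plan's own figures.** HR = ln(0.50)/ln(0.75) = 2.41. The stated formula gives (1.96 + 0.842)²/[(ln 2.41)² × 0.3 × 0.7] = 48.3, and 48/0.85 = 56.5, so 57. The figures reproduce. (The formula returns events, which the protocol labels patients. That is a separate matter, but it explains why the power figures in step 5 start below 80%.)

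**3. Events expected by T3.** Assume exponential hazards from the stated 2-year rates and T3 at month 5:

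- ctDNA-positive: 0.50^(5/24) = 0.866; ctDNA-negative: 0.75^(5/24) = 0.942.
- Probability of an event by T3: 0.3 × 0.134 + 0.7 × 0.058 = 0.081, or 3.9 of 48 and 4.6 of 57.
- Probability of an event by 2 years: 0.3 × 0.50 + 0.7 × 0.25 = 0.325. Early share: 0.081/0.325 = 25% (20% with T3 at month 4.0, 27% at month 5.5).

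This is used only for the number of early events, not for their ctDNA status.

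**4. Effect on the test when T3 status carries no information after T3.**

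*Simulation A:* 48 patients, 30% positivity among the later patients, equal hazards after T3 (24-month PFS 70% in both groups), and k patients failing at or before T3. Log-rank rejection at nominal 5%, clock from CCRT start:

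| Share of early failures ctDNA-positive | k = 3 | k = 5 |
|---|---|---|
| 60% | about 8% | about 13% |
| 80% | about 12% | about 24% |
| 100% | about 18% | about 40% |

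Repeat runs moved these by up to about 3 percentage points. With k = 0, rejection is 4.5% to 4.9%. If early failures have the same 30% positivity as everyone else, it is about 5%.

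*Simulation B:* overall positivity fixed at 30%, 2-year event rate 32.5%, and a stated proportion with progression at the T3 scan:

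| Progression at T3 | Share positive | HR from CCRT start | Rejection |
|---|---|---|---|
| 5% | 60% / 80% / 100% | 1.25 / 1.46 / 1.59 | 8% / 13% / 19% |
| 10% | 60% / 80% / 100% | 1.54 / 2.15 / 2.78 | 16% / 33% / 53% |

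The landmark analysis of the same scenarios gives HR 0.95 to 1.01 and 5% to 6% rejection.

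**5. Price of a landmark at month 5.** Schoenfeld power is Φ(√[D·p(1−p)] × ln HR − 1.96), with D events, positive share p and HR 2.41.

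- 57 patients, all events to month 24: D = 57 × 0.325 = 18.5, p = 0.30, power 41%.
- 57 patients, events after T3 only: D = 18.5 − 4.6 = 13.9, p = 0.3 × 0.866/(0.3 × 0.866 + 0.7 × 0.942) = 0.28, power 31%.
- 48 patients: 15.6 events and 36%, falling to 11.7 events and 27%.

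**The case against.** Five points can fairly be made for the plan.

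- **The event-free lead-in.** A reader might infer that the months before T3 in which analysed patients could not fail also inflate the hazard ratio. They do not. If every analysed patient is event-free at T3, the risk sets are unchanged, as the k = 0 result shows. The lead-in raises only the Kaplan-Meier 2-year PFS, and only if patients with earlier events are left out.
- **Worst-case size.** A reader might take 18% or 40% as the expected error rate. Those figures need every early failure to be ctDNA-positive. The protocol gives reason to doubt that: its limitations section cites 30-40% of patients testing negative even at baseline, and trace-positive results are not counted as positive in the primary analysis. This stands, and the smaller figures must be shown beside them.
- **Imputation.** A reader might infer that the plan imputes T3 status for patients who have already progressed or died. It does not say so. The sample size is stated in evaluable patients, which fits leaving out those without a T3 result, and such rules may sit in an analysis plan not shown. What stands is that the rule as worded could cover them.
- **The null.** If progressors at T3 are mostly positive, T3 status truly is associated with PFS as defined, so the rejections are not false in that narrow sense. This makes it a question of what the primary comparison estimates, and does not remove it.
- **Cost.** A landmark is not free, as step 5 shows.

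None of this removes the conflict. The time origin and the grouping time are both fixed in the article, so an analysis plan that followed them would reproduce the problem.

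**Conclusion.** The concern holds, limited to events at or before T3. As written, the primary comparison counts progression seen by the T3 scan as an outcome of T3 ctDNA status, and only those events bias the hazard ratio as a measure of prognosis after T3. The size depends on two quantities the protocol does not give: how many patients fail by T3, and what share of them are ctDNA-positive. Rejection under no later effect ranges from about 5%, when that share is no higher than in other patients, to about 40% with 5 failures, all positive. Three or four early failures among 48 is a plausible count, since the protocol's own rates with exponential hazards give 3.9 by month 5. Because this affects what the primary result means, it should be settled before recruitment, planned for January 2027.

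**What to change.** 1. Make the primary comparison a T3 landmark analysis in patients alive and progression-free on the T3 scan. Start the clock at the later of the T3 sample and T3 scan dates: each has a ±2-week window, so they could lie up to 4 weeks apart.
2. State from which date 2-year PFS runs. Sampling ends 24 months after CCRT completion, about 21 months after T3, so a full 24 months from the landmark would rely on later clinical and imaging follow-up.
3. State that T3 ctDNA status is not imputed for patients with an event at or before T3. Report them separately, with their T0 to T2 results.
4. Keep PFS from CCRT start as a description of the whole cohort, supported by a Cox model with time-updated ctDNA status.
5. Recalculate and restate power on post-T3 events.

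The wording and code are cheap. The real cost is that about 20% to 27% of expected 2-year events (exponential assumption) leave the primary comparison. At the planned 57 patients and HR 2.41, that takes power from about 41% to about 31%.

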## Introduction

Cervical cancer remains a substantial global health challenge, with an estimated 662,044 new cases and 348,709 deaths occurring worldwide in 2022, representing the fourth most common malignancy and cause of cancer-related mortality in women (1). The burden disproportionately affects low- and middle-income countries, where 90% of cervical cancer deaths occur, primarily reflecting inequities in access to human papillomavirus (HPV) vaccination, screening programs, and definitive treatment services (2). Notably, China and India together account for 42% of global incident cases and 39% of deaths, with projections indicating a 56.8% increase in new cases and an 80.7% rise in mortality by 2050 if current rates remain unchanged (1).

Locally advanced cervical cancer (LACC), encompassing International Federation of Gynecology and Obstetrics (FIGO) 2018 stages IB2 through IVA, constitutes a considerable proportion of newly diagnosed cases in resource-limited settings (3). Concurrent chemoradiotherapy (CCRT) with platinum-based chemotherapy has been established as the standard therapeutic approach for LACC since 1999, demonstrating significant survival benefits in landmark randomized controlled trials (4). Despite advances in treatment delivery techniques including intensity-modulated radiotherapy and image-guided brachytherapy, approximately 30-40% of patients receiving CCRT experience treatment failure, manifesting as incomplete response, residual disease, or early recurrence within two years (5, 6). This substantial recurrence rate underscores the urgent need for reliable biomarkers capable of identifying high-risk patients who may benefit from treatment intensification or alternative therapeutic strategies.

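### Recurrence is defined as new lesions after complete response, yet it is the sole reference outcome for ctDNA accuracy, so failures that never reached complete response count as non-recurrences and bias PPV down and NPV up

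*Protocol article*

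**What the plan says.** All references are to the protocol article.

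- **Outcome measures, primary outcome.** PFS has three separate components. The first is "first documented disease progression (according to RECIST 1.1 criteria on imaging studies or histopathologic confirmation". The second is "disease recurrence (appearance of new lesions after achieving CR". The third is death from any cause. Recurrence is defined nowhere else.
- **Outcome measures, secondary outcome (4).** The aim is "Predictive performance of HPV ctDNA for disease recurrence". The measures are "sensitivity (proportion of patients with recurrence who have detectable ctDNA", "specificity (proportion of patients without recurrence who have undetectable ctDNA", PPV as "probability of recurrence given detectable ctDNA" and NPV as "probability of no recurrence given undetectable ctDNA", plus the AUC. No ctDNA time point is named, and the item is not limited to patients who reached CR.
- **Statistical analysis.** The same measures are again tied to recurrence, and cut-offs for continuous ctDNA are chosen by Youden's index.
- **Outcome measures, secondary outcome (5).** Residual disease at 3 months appears here, in the agreement of ctDNA with imaging (kappa and contingency tables).
- **Introduction.** Treatment failure after chemoradiotherapy is described as "manifesting as incomplete response, residual disease, or early recurrence within two years", so residual disease and recurrence are distinct forms of failure.

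**The concern.** A reference outcome should contain the events that the marker is meant to predict. Here it contains only relapse after CR. A patient with partial response, stable disease or progression who never reaches CR cannot have a recurrence as defined, even if she later meets RECIST progression or dies of her cancer. She stays in the tables as a patient without the outcome.

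This distorts the results in two directions. A positive ctDNA result in such a patient was right about her prognosis but is scored as an error. A negative result was wrong but is scored as correct. The second matters as much as the first, because the Strengths section suggests that sustained undetectable ctDNA might support lighter follow-up, and NPV is the figure a reader would look to for that. The ROC curve and the Youden cut-off use the same outcome and inherit the problem.

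**Working it through.** **Plan's own figures.** The article states no expected sensitivity, specificity, PPV or NPV, so there is none to reproduce. The inputs come from Sample size calculation: 48 evaluable patients, 30% ctDNA-positive at T3, and 2-year PFS of 50% (positive) and 75% (negative). They agree with the stated hazard ratio: ln(0.50)/ln(0.75) = 2.41. The number 48 only sets the cell counts; the percentages below do not depend on it.

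**Where each patient falls under the stated definition**

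| Course | ctDNA-positive | ctDNA-negative |
|---|---|---|
| CR, then new lesions | true positive | false negative |
| Never CR, then progression or death from disease | false positive | true negative |
| No failure | false positive | true negative |

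The second row is the problem: it is scored in the same way as the third.

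**If every failure counts**

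- Positives: 48 × 0.30 = 14.4, with 14.4 × 0.50 = 7.2 failures.
- Negatives: 48 − 14.4 = 33.6, with 33.6 × 0.25 = 8.4 failures and 25.2 without failure.
- PPV = 7.2/14.4 = 50%. NPV = 25.2/33.6 = 75%.
- Sensitivity = 7.2/(7.2 + 8.4) = 46%. Specificity = 25.2/(25.2 + 7.2) = 78%.

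**If only recurrence after CR counts.** Let r be the share of failures that never reached CR among positives, and s the same share among negatives. The documents give neither, so both are assumed. Then:

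- PPV = 0.50 × (1 − r)
- NPV = 1 − 0.25 × (1 − s)
- Sensitivity = 7.2(1 − r) / [7.2(1 − r) + 8.4(1 − s)]
- Specificity = [33.6 − 8.4(1 − s)] / [48 − 7.2(1 − r) − 8.4(1 − s)]

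PPV falls for any r above zero: r = 0.3, 0.5 and 0.7 give 35%, 25% and 15%. NPV rises for any s above zero: s = 0.2 gives 1 − 0.25 × 0.8 = 80%.

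| r | s | PPV | NPV | Sensitivity | Specificity |
|---|---|---|---|---|---|
| 0 | 0 | 50% | 75% | 46% | 78% |
| 0.5 | 0 | 25% | 75% | 3.6/12.0 = 30% | 25.2/36.0 = 70% |
| 0.5 | 0.2 | 25% | 80% | 3.6/10.32 = 35% | 26.88/37.68 = 71% |
| 0.5 | 0.5 | 25% | 88% | 3.6/7.8 = 46% | 29.4/40.2 = 73% |
| 0 | 0.5 | 50% | 88% | 7.2/11.4 = 63% | 29.4/36.6 = 80% |

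Only PPV and NPV have a fixed direction. Equal shares leave sensitivity at 46%. If the never-CR failures are all in negatives, sensitivity and specificity both rise.

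**The case against.** The strongest reply is that the definition sits in a parenthesis inside the PFS sentence, and item (4) does not refer back to it. Usage is also loose: the lead-time outcome speaks of imaging-detected recurrence in patients who experience progression. The authors may have meant any failure. That is possible, but no text says so. When the NGS paragraph of the ctDNA detection section means both, it names recurrence and progression side by side. Two readings that give a PPV of 50% or 25% are reason enough to settle the wording.

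A second reply is that residual disease has its own outcome in item (5), and that separating detection of residual disease from prediction of recurrence is a sound design. It would be, if item (4) were limited to patients in CR. It is not, so patients who never reached CR remain in its denominators, and a kappa in item (5) does not take them out.

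Three stronger readings are tempting, but the documents do not support them.

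- **Every ctDNA-positive patient with persistent disease at T3 is a false positive.** Item (4) names no time point, and a partial response at T3 may later become a CR followed by relapse, which does count as recurrence. The misclassification concerns patients who never reach CR.
- **Sensitivity and specificity must be biased downward.** The table shows that their direction depends on r and s.
- **The PFS definition is also faulty.** RECIST progression is a PFS event in its own right, and the progression component also accepts histopathologic confirmation. How to count persistent disease in PFS is open to debate; it is not an error here.

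**Conclusion.** The concern holds for secondary outcome (4) and the matching sentence in Statistical analysis. As written, the reference outcome leaves out disease failures that never passed through CR but keeps those patients in the denominators. PPV is then biased down and NPV up, relative to disease failure.

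In the illustration PPV falls from 50% to between 35% and 15%, and NPV rises from 75% to 80%. These sizes rest on the assumed never-CR shares, on full 2-year follow-up, and on treating every PFS failure as a disease event although PFS includes death from any cause. Persistent disease that neither progresses nor leads to death is not in the planning rates, so the illustration does not cover it. The directions for PPV and NPV need only a nonzero share in the group concerned.

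The primary PFS comparison is not put in doubt by this point.

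**What to change.** In Outcome measures, secondary outcome (4), and the matching sentence of Statistical analysis:

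1. Replace recurrence as the reference outcome by disease failure by 24 months, with the starting date of the 24 months stated. Disease failure means RECIST 1.1 progression, recurrence after CR, or persistent disease documented by the scheduled imaging, with biopsy where available. Biopsy should not be required: Clinical evaluation and imaging plans it only for recurrence seen on imaging, and only where feasible.
2. Name the ctDNA time point that serves as the test: T3, as in the primary comparison.
3. Add a secondary table limited to patients in CR at T3, for prediction of later recurrence. This keeps the narrower question in a group where it is well defined.

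No change to the PFS definition is needed. The cost is a few lines of wording and a small amount of extra tabulation from imaging already scheduled. The drawback is some overlap with item (5), since persistent disease at 3 months would enter both. Recruitment is planned to begin in January 2027, so the wording can be settled before the first patient enters.
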